### Sample size

Sample size calculations were based on published data [5,14,16]. The mean differences in WOMAC scores before and after treatment with the integrative TCM approach, counter osteophytes capsule, Fufang Zijin patch, acupuncture and Tuina are 11 (SD = 5), 12 (SD = 6), 9.34 (SD = 4.09), 10.17 (SD = 3.85) and 8.89 (SD = 4.32), respectively. Using these data we estimated that 420 patients would be sufficient to give 0.8 power at 0.05 alpha level. Allowing for dropout, we plan to enroll 500 patients.

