### Efficacy analysis

The primary efficacy analysis will be based on the full analysis set, defined as all randomized subjects who have baseline and at least one post-baseline efficacy assessment. OA trials are prone to dropouts related to treatment (e.g., inadequate response or intolerance) and because such dropouts will not be at random, thus standard imputation methods are inapplicable. Therefore, we will conduct sensitivity analysis described below wherein missing data are imputed to increasingly adverse degrees to explore whether the primary result still stands. As a supportive analysis, efficacy will also be assessed based on the per protocol set, defined patients in the full analysis set who have no major protocol violation. Statistical comparisons for total and subscale scores based on the WOMAC will be made using a repeated-measure mixed model with terms for treatment, day, center, and baseline value as covariate. The within-subject covariance structure will be assumed unstructured. Treatment-by-day and day-by-baseline interactions will be included in order to compare the treatment difference at each assessment time point as well as for the average across time points. The treatment difference and its 95% confidence interval will be estimated from this model. The same approach will be used for analyzing the Patient Global Assessment of OA condition and the Investigator Global Assessment of OA condition. A similar approach will be used for analysis of Patient and Investigator Global Assessments of response to treatment, but without inclusion of a baseline covariate and associated interaction terms.

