### Sensitivity analysis

In this analysis missing data for patients prematurely discontinuing from the trial (or for patients for other reasons not included in the full analysis set) are generated by random draw from the completer patient data, then adjusted as described below. The analysis is described for a situation where treatment A is statistically significantly superior to treatment B by the primary efficacy analysis. The treatment effect is the difference of the WOMAC change in the treatment A and the WOMAC change in treatment B. Call this treatment effect difference D. Four scenarios are investigated, corresponding to the loss of 25%, 50%, 75%, and 100% of the treatment effect difference. Patients that prematurely discontinued from treatment A will have their WOMAC change values determined by random draw (with replacement) from the treatment A completers, then these values are adjusted downward by 1/8*D, 2/8*D, 3/8*D, then 4/8*D, for the 1^st^, 2^nd^, 3^rd^, and 4^th ^scenario, respectively. Treatment B dropouts will have their random draw values adjusted upward sequentially by the same factors (1/8*D, 2/8*D, 3/8*D, then 4/8*D). The four scenarios, therefore, are:

#1-Assuming loss of 25% of the treatment effect; this is the least adverse scenario.

#2-Assuming loss of 50% of the treatment effect seen in completers.

#3-Assuming loss of 75% of the treatment effect seen in completers.

#4-Assuming loss of 100% of the treatment effect; this is the most adverse scenario.

Because the analysis involves stochastic variables, it will be repeated 100 times in order to better estimate the means and approximate 95% confidence intervals.

The following treatment comparisons will be performed based on the repeated measures mixed model and sensitivity analysis:i) Comparison at each of Days 0, 14, and 28;ii) Comparison of the Day 14 and 28 averages, using the time-averaged Day 14 and 28 scores estimated within the model framework;iii) Comparison of the average over all post-treatment days, using the time-averaged Day 14 and 28 scores estimated within the model framework;iv)All statistical tests will be two-sided. The primary endpoint and key secondary endpoints will be tested.

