## Discussion

The biggest limitation of this study is the lack of placebo control. It should be noted that the aim of this trial is not to estimate the efficacy of treatments used, but to demonstrate that individually integrated TCM approach is superior to individual component alone. This aim arises from clinical experience. The components of these treatments have been used for centuries. TCM has over 2000 years' application in China, usually as "one method applied in a whole course of treatment". However, even though the individual approach, based on different features of OA, is recommended, there is no evidence that it is superior to a treatment component used alone.

In an OA trial, a statistically significant result might be due to the dropout pattern rather than a true treatment effect, so we are attempting to collect data at the time of discontinuation to enable better comparisons of those completing versus those discontinuing. Additionally, we are conducting a formal sensitivity analysis using imputed data for discontinued patients to determine whether a positive result remains positive in scenarios where part or all of the treatment effect difference seen in the completers is lost in the dropout patients. To our knowledge, this is the first trial in a chronic symptomatic disorder to explicitly specify this type of sensitivity analysis to address trial dropouts.

Our results will be conditional on the population recruited, and the patients we recruited, requiring pain intensity of 20 mm or more on visual analogue scales (VAS), may have larger or smaller responses to treatment compared to those without such a restriction. For example, it was recently shown that use of a "flare" to define trial eligibility in OA alters, on average, response to treatment [17]. Another limitation is no double-blinding. Although it is difficult to carry out double-blinding in this design, we blind those clinicians conducting the assessments to decrease possible bias. The study also lacks long-term follow-up and evaluation. However, the duration chosen in the present study is consistent with acute OA flare episodes; and the study is long enough to document a rapid onset of a treatment modality and its efficacy sustained for 4 weeks. The protocol has a provision for rescue medication although its use is discouraged.

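### The harshest dropout scenario only equalises dropouts between arms, so it is a mild bound that ignores unequal dropout; an asymmetric tipping-point series should be added

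*Protocol article*

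**What the plan says.** The protocol article, Efficacy analysis, states that osteoarthritis trials lose patients for reasons tied to treatment, such as poor response or poor tolerance, and that this loss is not random. It therefore plans an analysis in which "missing data are imputed to increasingly adverse degrees to explore whether the primary result still stands".

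The Sensitivity analysis section gives the recipe for a comparison in which A has been found significantly better than B:

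- D is defined thus: "The treatment effect is the difference of the WOMAC change in the treatment A and the WOMAC change in treatment B".
- "Patients that prematurely discontinued from treatment A will have their WOMAC change values determined by random draw (with replacement) from the treatment A completers", and then "these values are adjusted downward by 1/8*D, 2/8*D, 3/8*D, then 4/8*D".
- "Treatment B dropouts will have their random draw values adjusted upward sequentially by the same factors".
- The four scenarios are labelled as losing 25%, 50%, 75% and 100% of the effect. The last reads "4-Assuming loss of 100% of the treatment effect; this is the most adverse scenario".
- The draw is repeated 100 times. No rule for combining the variances is given.

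The main Discussion warns that a significant result may arise from the pattern of dropout. It says the scenarios test whether a positive finding holds when "part or all of the treatment effect difference seen in the completers is lost in the dropout patients".

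**The concern.** The plan expects dropouts to be patients who did badly. Yet every imputed value starts from a completer of the same arm and moves by no more than D/2. In scenario 4 both groups of dropouts land midway between the two completer means, so A dropouts keep most of a completer's gain and B dropouts are placed above B completers. No scenario lets A dropouts fare worse than B dropouts, and the share lost from each arm has no separate influence.

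What is at stake is the question that the Discussion itself raises. If the integrated arm lost more patients, or lost patients who did worse, a significant difference among completers could be a dropout artefact. The four scenarios could still report most of it as intact.

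**Working it through.** **Inputs**
- Mean change (SD), from Sample size: integrated 11 (5), patch 9.34 (4.09), Tuina 8.89 (4.32).
- Dropout: Sample size says "we estimated that 420 patients would be sufficient to give 0.8 power at 0.05 alpha level" and plans to enrol 500. The implied allowance is 1 − 420/500 = 16%, or 84 completers of 100 per arm. No rate is stated, so 16% is an assumption; 30% is shown as well.
- Simplifications: larger change means more improvement, D is the completer difference, and the endpoint is a single change score. The mixed model would also use Day 14 values from patients who leave later.

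**1. Reproducing the labels.** In scenario k (1 to 4), A dropouts average mA − (k/8)D and B dropouts average mB + (k/8)D. Their difference is D − (k/4)D = D(1 − k/4). The loss among dropouts is 25%, 50%, 75% and 100%, as labelled.

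**2. Effect over all randomised patients.** With dropout fractions pA and pB:

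[mA − pA(k/8)D] − [mB + pB(k/8)D] = D[1 − (k/4)(pA + pB)/2]

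- At 16% in each arm: 0.96, 0.92, 0.88 and 0.84 of D.
- At 30% in each arm, scenario 4: 0.70 of D.
- Only pA + pB enters. Simulated splits of 6%/26% and 26%/6% also gave 0.84 of D.

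**3. Where scenario 4 puts the dropouts**
- Integrated versus Tuina: D = 11 − 8.89 = 2.11. Dropouts in both arms average 11 − 2.11/2 = 9.945, which is 90% of the integrated completers' 11 and above the Tuina completers' 8.89. Overall effect: 0.84 × 2.11 = 1.77.
- Integrated versus patch: D = 1.66. Dropouts average 10.17, which is 92% of 11 and above 9.34. Overall effect: 0.84 × 1.66 = 1.39.

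**4. Less favourable patterns (illustrations)**
- Tuina, 24% versus 8% dropout, no improvement in any dropout: 0.76 × 11 − 0.92 × 8.89 = 8.36 − 8.18 = 0.18. Scenario 4 still gives 2.11 × (1 − 0.32/2) = 1.77.
- 16% in each arm, no improvement in integrated dropouts, comparator dropouts like their completers: 0.84 × 11 − 8.89 = 0.35 (Tuina) and 0.84 × 11 − 9.34 = −0.10 (patch).
- 16% in each arm, no improvement in any dropout: 0.84 × 11 − 0.84 × 8.89 = 1.77, the same mean as scenario 4.

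**5. Which significant results fail scenario 4.** The answer depends on the unstated variance rule.
- Imputed values counted as observed (100 per arm): the completer z must reach 1.96/√0.84 = 2.14, p about 0.033.
- Standard error kept at the completer level: 1.96/0.84 = 2.33, p about 0.020.

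At 80% power z is centred at 1.96 + 0.84 = 2.80. The share of significant results that pass is P(z > 2.14)/0.80 = 93%, or P(z > 2.33)/0.80 = 85%, so 7% to 15% fail. Simulation gave 93% with averaged standard errors and 88% with Rubin's rules. At 50% power 14% to 29% fail; at 30% dropout and 80% power, 15% to 37%.

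**6. What a tipping point would show.** Shift only A dropouts down by δ: effect = D − pA·δ. For Tuina at 16% dropout, the standard error is √[(25 + 18.66)/100] = 0.661, or √[(25 + 18.66)/84] = 0.721. Held fixed, significance is lost at δ = (2.11 − 1.96 × 0.661)/0.16 = 5.1 or (2.11 − 1.96 × 0.721)/0.16 = 4.4 points. The plan's largest shift of A dropouts is 2.11/2 = 1.06 points.

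**The case against.** The strongest reply is that the plan misstates nothing. It ranks its own four scenarios from least to most adverse, and the Discussion makes clear that the percentages concern dropouts. Read that way, the 100% is exact. This stands: there is no calculation error, only a label that can be taken for more than it is. The wording on completers appears in scenarios 2 and 3 but not in 1 and 4.

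A reader might infer that the scheme passes almost any significant result. Step 5 does not support that: a noticeable minority fails, and more fail as dropout rises.

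A reader might also infer that the milder scenarios strengthen the result. That happens only if imputed values are counted as real observations. The article does not say so and may leave the rule to a fuller document.

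Nor is this the plan's only provision on dropout. Withdrawal allows a final WOMAC score to be requested and separates adverse events from insufficient response. The Discussion says data will be sought when patients stop. These measures help, but the Sensitivity analysis does not say how such scores enter the imputation.

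Finally, the patterns in step 4 are not predictions. The documents do not say that the integrated arm will lose more patients or that its dropouts will do worse. True, but the plan's stated aim is to find out whether such a pattern could explain the result, and none of its scenarios can represent one.

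**Conclusion.** The point holds as a limit on what the four scenarios can show. Scenario 4 removes the average dropout fraction of D and no more: 16% at the inferred allowance, 30% if dropout is 30%. It does not respond to unequal dropout and never places A dropouts below B dropouts. Given the plan's own view that dropout is related to treatment, it is a mild bound. Surviving it does not rule out the artefact named in the Discussion.

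The formula is exact for a single change score with D taken as the completer difference; the point values rest on the planning means. The primary estimate, test and population are unaffected. This is a cheap improvement to a sensitivity analysis, not a must-fix.

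**What to change.** - Keep the four scenarios. State that the percentages refer to the effect lost among dropouts, and call scenario 4 the most adverse of these four only.
- Add a tipping-point series: leave B dropouts unshifted, move A dropouts down beyond D/2 in steps until they show no change from baseline, and report the shift in WOMAC points at which significance is lost.
- Add a scenario with no change from baseline for dropouts in both arms. On the mean it adds information only when dropout is unequal. It is a stress test only when A loses more patients: with 8% versus 24% it would give 0.92 × 11 − 0.76 × 8.89 = 3.36 against Tuina, which favours A. The tipping-point series is therefore needed as well.
- Call a result robust only if it survives the no-change scenario and the tipping shift is implausibly large, with that judgement criterion set before results are seen.
- Use WOMAC scores obtained at withdrawal where they exist, and combine the 100 repetitions with between-imputation variance included.

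The cost is a few more analysis runs and some wording; no new data are needed. The downside is that a positive result may have to be reported as less robust.

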### Data integrity and management

Data will be stored electronically on a database with secured and restricted access. Data transfer will be encrypted and any information capable of identifying individuals removed.

### Withdrawal

A participant will be considered to have withdrawn from the trial when consent is revoked (except to ask permission for a determination of a final withdrawal visit WOMAC score) or if the participant cannot be contacted or located. If this occurs, no further assessments will be performed. Participants will not be withdrawn from the trial for protocol violations. Withdrawal due to adverse event should be distinguished from withdrawal due to insufficient response. When a subject withdraws due to a serious adverse event, the serious adverse event must be reported in accordance with the reporting requirements.

### Monitoring

The trial will be overseen and monitored by a program manager. The program manager will visit each site to examine trial procedures, ensure data quality and monitor compliance with the trial protocol.

## Discussion

The biggest limitation of this study is the lack of placebo control. It should be noted that the aim of this trial is not to estimate the efficacy of treatments used, but to demonstrate that individually integrated TCM approach is superior to individual component alone. This aim arises from clinical experience. The components of these treatments have been used for centuries. TCM has over 2000 years' application in China, usually as "one method applied in a whole course of treatment". However, even though the individual approach, based on different features of OA, is recommended, there is no evidence that it is superior to a treatment component used alone.

In an OA trial, a statistically significant result might be due to the dropout pattern rather than a true treatment effect, so we are attempting to collect data at the time of discontinuation to enable better comparisons of those completing versus those discontinuing. Additionally, we are conducting a formal sensitivity analysis using imputed data for discontinued patients to determine whether a positive result remains positive in scenarios where part or all of the treatment effect difference seen in the completers is lost in the dropout patients. To our knowledge, this is the first trial in a chronic symptomatic disorder to explicitly specify this type of sensitivity analysis to address trial dropouts.

Our results will be conditional on the population recruited, and the patients we recruited, requiring pain intensity of 20 mm or more on visual analogue scales (VAS), may have larger or smaller responses to treatment compared to those without such a restriction. For example, it was recently shown that use of a "flare" to define trial eligibility in OA alters, on average, response to treatment [17]. Another limitation is no double-blinding. Although it is difficult to carry out double-blinding in this design, we blind those clinicians conducting the assessments to decrease possible bias. The study also lacks long-term follow-up and evaluation. However, the duration chosen in the present study is consistent with acute OA flare episodes; and the study is long enough to document a rapid onset of a treatment modality and its efficacy sustained for 4 weeks. The protocol has a provision for rescue medication although its use is discouraged.

OA diagnosis is made based on objective radiological criteria along with excluding inection or gout, and it made using the medical history and physical exam. The WOMAC index is a validated scale that uses 24 parameters to assess OA of the hip or knee with focus on Pain, Stiffness, Physical Function, Social Function and Emotional Function [18,19]. The design of this study is consistent with both global clinical research standards and use of TCM criteria for evaluating efficacy and safety. One important principle guiding TCM therapy is to use drug treatment according to "Syndromes". Syndrome is different from the disease name, since it is a summarized analysis of the symptom data from patients' whole situation using TCM methods. It may not only include local symptoms which are part of the disease but also symptoms from the whole body situation. Given the differences in the whole body situation in different people, it is natural that OA, a kind of disease, has different Syndromes. In TCM, OA is known as Bi, Wei, Ganshen kuixu, or Jinmai yuzhi Syndrome and so on [20].

WOMAC questionnaires are detailed in the description of local symptoms of OA, while the Syndromes questionnaires more emphasizes the body's whole situation. Thus, the result of this research could also provide information on the correlation of symptoms-analysis gathered from WOMAC and Syndromes of TCM in different phases (mild, moderate or severe) of OA which may be helpful for predicting severity of OA using TCM methods.

Given the use of two manipulative methods (acupuncture, Tuina) in this study, patients' compliance and response to treatment is critical to the treatment effect. WOMAC subscale analysis will provide information on which OA symptom (pain, stiffness, or function) was more responsive to which treatment. Since this is an East meet West study, outcome measures capture both OA symptoms and the whole body TCM assessment according to TCM theory. We also include a standard quality of life measure, the SF-36, as in many other OA trials [21,22].

## List of abbreviations

(OA): Osteoarthritis; (RCT): randomized controlled trials; (TCM): Traditional Chinese Medicine; (WOMAC): Western Ontario McMaster Universities Osteoarthritis Index; (SF-36): short-form 36; (ACR): American College of Rheumatology; (SOP): Standard Operation Procedure; (VAS): visual analogue scales.
